#### Secondary hypotheses

We will also test multiple secondary hypotheses to understand the additional impact of our strategy implementation. These include the following:
The rate of surgical site infection will be no different prior to the study versus order set and/or enhanced facilitation groups.The rate of *Clostridioides difficile* infection will be improved when comparing control versus baseline, and experimental condition versus control or baseline.

A statistical model analogous to model (1) will be used for the secondary outcomes analyses, where *π*_*itkl*_ will be replaced by the rate of SSI or CDI and implementation outcomes, respectively.

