Unadjusted analysis through model (1) will be conducted, and an adjusted model will be developed. The following data elements will potentially be included in this model: hospital, age, surgical subspecialty (e.g., orthopedics, ENT, etc.), type of procedure, duration of hospitalization, and co-morbidities. The estimated intervention effect will be reported as odds ratio with 95% CIs and *p* values. The tests will be two-sided and the significance level will be set at 0.05. The statistical package SAS 9.4 will be used for all statistical calculations.

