#### Power estimates

The sample size calculation is based on the primary outcome only. We utilized the sample size formula for repeated cross-section stepped-wedge cluster randomized trials from Hooper and colleagues [41]. This formula depends on the intra-cluster correlation (ICC), cluster auto-correlation, number of groups, number of steps, and the number of patients at each cross-section, where cluster auto-correlation is defined as the correlation between two population means from the same cluster at different times.

Our prior work from 32 children’s hospitals determined rates of inappropriate postoperative antibiotic use with an ICC of 0.121 and cluster auto-correlation of 0.328 [42]. The proposed experimental intervention is expected to decrease unnecessary postoperative antibiotic use rates from 33% to 13-18%. A total sample of 46 cases per step per hospital and 9 hospitals achieves 80% power to detect the inappropriate antibiotic rate difference of 0.20 between intervention (13%) and control groups (33%) at the significance level of 0.05, assuming an ICC of 0.121 and cluster auto-correlation of 0.328.

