A strength of this study is the use of a cluster randomized stepped-wedge design [26]. This design allows for a greater number of hospitals to receive both the control and intervention arms of the study than would otherwise be feasible with a standard randomized controlled trial. Furthermore, hospitals will be evaluated over 3 years, allowing for a better understanding of long-term effects of these interventions.

Several limitations are present in this study. First, the specific clinical outcomes from surgeries impacted by our implementation strategies may not be directly followed. Rather, we will be capitalizing on a separate data collection effort, NSQIP-P. While this means that some surgeries impacted by implementation strategies will be assessed, some will not, which may decrease the effect size observed. Second, this study will be unable to determine the direct impact of the de-implementation of postoperative antibiotic prophylaxis on antibiotic resistance, as SSI rates are infrequent, and the amount of time needed to discern a change in bacterial resistance patterns is much longer than the duration of this study. Lastly, this study will be done in a tertiary-care children’s hospitals and therefore may not be generalizable to other clinical settings such as community hospitals or outpatient clinics.

The addition of facilitation training of the ASP team may not result in a greater reduction of unnecessary postoperative antibiotic use than order set review and modification alone. If this occurs, an interrupted time-series analysis will be conducted evaluating the baseline data until the implementation of the order set to determine if the order set change impacted the use. Since order set change and modification is a simpler, less resource intense intervention, this result would be favorable and allows for more rapid dissemination. An important strength of the study is the use of the SHARPS Collaborative and NSQIP-P which will allow for immediate dissemination of the results to many additional hospitals.

Rigorously assessing de-implementation strategies is essential in providing high-value medical care. As clinical innovations advance medicine, routine, common practices that lack benefit and result in harm must be eliminated. The challenges to de-implementing evidence-based guidelines are different and therefore, need dedicated trials, like the OPerAtiC trial, to be conducted.

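### The surgical site infection hypothesis is one of no difference, but the only planned analysis is a two-sided difference test with no margin, so a non-significant result cannot support it

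*Protocol article*

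**What the plan says.** All places are in the protocol article.

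- **Secondary hypotheses.** Among the hypotheses to be tested: "The rate of surgical site infection will be no different prior to the study versus order set and/or enhanced facilitation groups". The method follows: "A statistical model analogous to model (1) will be used for the secondary outcomes analyses".
- **Primary hypothesis.** For model (1), "The tests will be two-sided and the significance level will be set at 0.05", and "The estimated intervention effect will be reported as odds ratio with 95% CIs and *p* values". The model's treatment indicator takes two values, intervention or control.
- **Study design.** All nine hospitals begin the control strategy together at the start of step 0. Facilitation then starts in three groups of three hospitals, at steps 1, 2 and 3.
- **Power estimates.** "The sample size calculation is based on the primary outcome only". Facilitation is "expected to decrease unnecessary postoperative antibiotic use rates from 33% to 13-18" per cent.
- **Discussion.** Antibiotic resistance cannot be assessed, in part "as SSI rates are infrequent". If facilitation gives no greater reduction than order sets alone, an interrupted time series will check whether the order set change affected use. The article continues: "Since order set change and modification is a simpler, less resource intense intervention, this result would be favorable and allows for more rapid dissemination".

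**The concern.** Surgical site infection is the outcome that checks whether withdrawing postoperative prophylaxis does harm. The hypothesis about it is that nothing changes. A two-sided difference test takes no difference as its null, so the data can only count against the hypothesis or fail to do so. With a rare outcome and no sizing, failing to reject is likely even if infections rise. Without a margin set beforehand, nothing in the article says how narrow the interval must be before absence of an increase may be concluded.

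The same logic arises, less sharply, in the Discussion. A primary result that shows no added benefit from facilitation leads to a favourable reading of order sets, although a missed benefit and an absent benefit can look alike.

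**Working it through.** **Method.** Generalised least squares variance for a repeated cross-section stepped wedge, with 3 sequences of 3 hospitals and fixed period effects. I use six 6-month periods: the trial lasts 3 years, and the 24 and 18 months of exposure given for clusters 2 and 3 fit six periods.

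For hospital-period means of m cases, with σ² = p(1−p), ICC ρ and cluster auto-correlation r:

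- variance of one mean: σ²[ρ + (1−ρ)/m]
- covariance of two periods in the same hospital: σ²ρr
- Var(δ) = last diagonal element of [Σ Z′V⁻¹Z]⁻¹ over the nine hospitals, where Z holds the period indicators and the treatment indicator
- power = Φ(|δ|/SE − 1.96); 95% half-width = 1.96 × SE

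**Step 1: the plan's own figure.** From Power estimates: 33% vs 13%, m = 46, ρ = 0.121, r = 0.328. σ² = (0.33×0.67 + 0.13×0.87)/2 = 0.1671, and SE = 0.0713. Power = Φ(0.20/0.0713 − 1.96) = 80.0%. With m = 45 it is 79.9%, so 46 is the smallest m that reaches 80%. The stated figure reproduces. (Four periods would give 77.3%.)

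**Step 2: infection, facilitation versus order set.** The article gives no infection rate, ICC or auto-correlation for this outcome, so all are assumed. The ceiling of 750 cases per step is 1500 per year ÷ 2, before exclusions.

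Central case: 2%, ρ = 0.005, m = 400, σ² = 0.02×0.98 = 0.0196.

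| r | SE (points) | 95% half-width (points) |
|---|---|---|
| 0.328 | 0.583 | 1.14 |
| 0.8 | 0.468 | 0.92 |

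Over 1–3% infection, ρ 0.001–0.01, m 200–750 and both values of r, the half-width runs from 0.42 (1%, 0.001, 750, r = 0.8) to 1.97 (3%, 0.01, 200, r = 0.328). In the central case an estimate of exactly zero would leave an upper limit of about 2.9% to 3.1% against 2%, so a rise of about half would not be excluded. That is one scenario within a nearly fivefold range.

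With only the 46 cases per step of the sample size statement, 2% infection, ρ from 0 to 0.02 and r = 0.328, the half-width is about 2.0 to 2.8 points. An estimate of zero would then not exclude a doubling.

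**Step 3: which contrast the model holds.** The infection hypothesis compares the period before the study with order sets and/or facilitation. Model (1) has one treatment parameter, facilitation versus control. Since every hospital starts order sets at the same moment, a pre-study contrast is fully aligned with calendar time, and no parameter of model (1) estimates it. The half-widths in step 2 therefore concern facilitation versus order set only.

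**Step 4: the Discussion's fallback.** Inputs as in step 1.

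| True facilitation rate (control 33%) | m | SE | Power | Missed |
|---|---|---|---|---|
| 13% | 46 | 0.0713 | 80.0% | 20% |
| 13% | 750 | 0.0650 | 86.7% | 13% |
| 18% | 46 | 0.0749 | 51.7% | 48% |
| 18% | 750 | 0.0683 | 59.3% | 41% |

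For 18%, σ² = (0.2211 + 0.1476)/2 = 0.18435. Extra cases help little because there are only nine hospitals.

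**The case against.** **No decision rule is stated.** A reader might infer that the plan will report p > 0.05 as proof of safety. No sentence says so. The article commits to odds ratios with 95% CIs, which would show an imprecise estimate, and an interpretation rule may exist in an analysis plan that is not shown. This stands against the stronger reading. It does not remove the mismatch: the article itself fixes the hypothesis and the type of test, and a CI supports no increase only against a margin chosen beforehand.

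**The Discussion does not rest on the primary test alone.** A reader might infer that it treats a null primary result as proof that facilitation is not needed. It does not say that. It adds an interrupted time series, and the favourable result can be read as including an order-set effect shown by that analysis. This too stands. What remains is narrow: the time series compares order sets with baseline, so it can show that order sets work but not that facilitation adds nothing.

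**The infection figures are assumed, and 48% is the weak end.** Both are true. The half-widths are scenarios, and at the design effect the miss rates are 20% and 13%. The mismatch itself depends on none of these numbers.

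**Infection is a secondary outcome.** The primary model, test and sample size are indeed unaffected.

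**Conclusion.** The point holds for surgical site infection: a no-harm hypothesis is paired with a two-sided difference test, without a margin or sizing, so the planned analysis can contradict the hypothesis but not support it. How much harm a non-significant result would leave open for facilitation versus order set depends on the assumed infection rate, ICC, auto-correlation and case numbers; under the central assumptions it is about a percentage point. The pre-study comparison named in the hypothesis has no counterpart in model (1).

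The Discussion passage is a secondary wording point. Under the plan's own inputs, a benefit at the weaker end of its expected range would be missed in four to five trials out of ten, so failure to show added benefit is not evidence that there is none.

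**What to change.** 1. **Infection, facilitation versus order set.** Before any infection data by condition are examined, state a justified non-inferiority margin on the scale that will be reported (odds ratio or risk difference). Conclude no increase only if the upper 95% limit lies below it; otherwise report the outcome as inconclusive. Data are drawn from the registry after each step, so the date on which the margin was fixed should be recorded.
2. **Infection, before the study versus during it.** Report a descriptive before-after estimate with its CI, and state that it is confounded with calendar time, unless a separate model is specified.
3. **Discussion.** Say what the interrupted time series can show about order sets. Describe an added benefit of facilitation as not shown, unless the 95% CI excludes a pre-stated smallest worthwhile reduction.

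The cost is wording, one agreed margin and one agreed smallest worthwhile reduction. No new data are needed. The price is that the infection result may have to be reported as inconclusive.

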### Implementation data

Process: Semi-structured interviews (see Supplemental file A for interview guide) will be conducted with a member of the ASP team at each site monthly through the duration of the trial. These interviews will be conducted virtually via zoom and will last ~30 min. We will assess the progress of the site in identifying, reviewing, and changing current surgical order sets and implementing new order sets that do not contain post-operative orders for antibiotics. Furthermore, information will be obtained regarding current barriers, and additional work being done to eliminate unnecessary post-operative antibiotics (e.g., stakeholder meetings).Outcomes:
*Acceptability, Appropriateness, Feasibility*: We will assess the acceptability, appropriateness, and feasibility of each strategy using psychometrically strong and pragmatic survey measures [39], which will be distributed once during each step. All members of the ASP team will complete these surveys regarding the intervention(s) currently being implemented by the ASP. Therefore, during control, participants will complete the surveys for acceptability, appropriateness, and feasibility in relation to changing order sets as an implementation strategy. During the intervention, participants will complete separate surveys to independently evaluate changing order sets and the use of facilitation techniques.*Penetration* will be measured as the number of order sets modified or newly created. These data will be collected monthly through the web-based semi-structured interview.*Health beliefs*: Once per step, each member of the antibiotic stewardship team will be asked three health belief questions modeled off the COM-B system [18]. These questions assess the participants’ belief in their capability, motivation, and opportunity to change post-operative order sets.

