## Statistical analysis plan

### Clinical outcomes

#### Primary hypothesis

Our primary hypothesis is that the experimental intervention of enhanced ASP facilitation will decrease the percentage of cases receiving unnecessary postoperative antibiotic prophylaxis from baseline more than the control intervention. To test this hypothesis, statistical model (1) will be used. With each cross-section consisting of *m* patients, we assume a model in which the logit of outcome for patient *i* at times *t* = 0, ⋯, *T* in hospital *k* = 1, ⋯, *K*, and cluster *l* = 1, 2, 3 is
1$$ \mathrm{logit}\left({\pi}_{itkl}\right)=\gamma +{\theta}_t+{A}_{lt}\delta +{x}_{kl}+{h}_{tkl}+{\varepsilon}_{itkl}, $$

where *π*_*itkl*_ is probability of percentage of unnecessary postoperative antibiotic prophylaxis, $$ {\varepsilon}_{itkl}\sim N\left(0,{\sigma}_{\mathrm{error}}^2\right) $$, $$ {h}_{tkl}\sim N\left(0,{\sigma}_{\mathrm{time}\mid \mathrm{clinic}}^2\right) $$, $$ {x}_{kl}\sim N\left(0,{\sigma}_{\mathrm{clinic}}^2\right) $$, with *ε*_*itkl*_, *h*_*tkl*_, and *x*_*kl*_ are all independent of one another, and
$$ {A}_{lt}=\left\{\begin{array}{c}1\ \mathrm{if}\ \mathrm{cluster}\ l\ i\mathrm{s}\ \mathrm{receiving}\ \mathrm{the}\ \mathrm{intervention}\ \mathrm{at}\ \mathrm{time}\ t\\ {}0\ \mathrm{if}\ \mathrm{cluster}\ l\ i\mathrm{s}\ \mathrm{receiving}\ \mathrm{the}\ \mathrm{control}\ \mathrm{at}\ \mathrm{time}\ t\kern2.5em \end{array}\right. $$

This hierarchical, multilevel model includes a fixed effect of time *θ*_*t*_, we set *θ*_0_ = 0. The parameter *δ* is the treatment effect; we assume that the treatment effect is maintained once the intervention has been initiated. The fixed effect *θ*_*t*_ must be estimated independently of the treatment effect so that a systematic change over time is not mistaken for an effect of treatment. The model also includes random effect, variation between clusters (*x*_*kl*_), and variation between times within a hospital (*h*_*tkl*_).

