### Implementation outcomes

A descriptive analysis will be conducted for the implementation outcomes. This study is not powered to assess group differences but rather to understand the pre-post facilitation training differences in implementation outcomes of feasibility, acceptability, and appropriateness. This evaluation will utilize a mixed methods design with a Qualitative + QUANITATIVE structure that serves the function of for complementarity [40].

The qualitative aspect of the study allows for an understanding of the processes associated with the study. The monthly phone calls will be coded using a deductive content analysis [25]. Identifying information from the interviews will be removed and the interviews will be coded based on context, facilitation and strategies, and outcomes. This will be informed by iPARIHS (context and facilitation), ERIC (strategies), and outcomes (Proctor) to develop the codes. The codes will allow for information to be indexed in these relevant areas of the study and will facilitate exploration of the relevant contextual factors, interventions, and outcomes related to the study. These interviews will be co-coded by two coders in order to increase reliability of coding. Any discrepancies in coding will be resolved through meetings and discussions. Further, any order sets developed or changed will be captured and counted through these monthly phone calls.

The generalized estimating equation (GEE) model with appropriate link function will be used to analyze the implementation outcomes, in which the correlation among the ASPs from the same cluster need to be considered. The autoregressive of first order as working correlation structure will be considered. The GEE model includes the group indicator, month, and the interaction term between group and month. The *p* values of the interaction term from type 3 analysis in the GEE model will be estimated to assess whether the outcome across all ASPs between two groups are different. Least square means for each outcome for each group will be estimated and the standard errors will be calculated within the use of GEE sandwich method when accounting for within-cluster correlation.

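### The implementation outcomes, including penetration, are given two different inferential analyses with no order of precedence

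*Protocol article*

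**What the plan says.** Two parts of the article's Statistical analysis plan address the implementation outcomes.

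- **Secondary hypotheses** (under Clinical outcomes): "A statistical model analogous to model (1) will be used for the secondary outcomes analyses", and in that model the probability term "will be replaced by the rate of SSI or CDI and implementation outcomes, respectively". Model (1), under Primary hypothesis, is a patient-level mixed model: "we assume a model in which the logit of outcome for patient". It has fixed time effects, random effects for hospital and for time within hospital, and one treatment parameter, δ. On that parameter the article says: "we assume that the treatment effect is maintained once the intervention has been initiated". On reporting, it says: "The estimated intervention effect will be reported as odds ratio with 95% CIs".
- **Implementation outcomes**: the section opens by calling the analysis descriptive and adds: "This study is not powered to assess group differences". It then says: "The generalized estimating equation (GEE) model with appropriate link function will be used to analyze the implementation outcomes". The GEE has first-order autoregressive working correlation, sandwich standard errors, and terms for group, month and their interaction. The type 3 p value of the interaction is to decide whether the two groups differ.

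The Abstract names penetration as the primary implementation outcome. Under Implementation data, penetration "will be measured as the number of order sets modified or newly created" and is collected monthly. Acceptability, appropriateness and feasibility come from surveys of stewardship team members once per step. Health-belief questions are listed there too.

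**The concern.** Both instructions are worded as what will be done. Neither is labelled main, sensitivity or exploratory. An analyst following the article would have two rules for the same outcome, and the rules differ in effect structure, tested term and interpretation.

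This matters most for penetration, because it carries the label of primary implementation outcome. If the two analyses disagree, the article gives no basis for saying which is the trial's answer. The descriptive label adds to the difficulty, because the same section then judges the group difference by a p value.

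**Working it through.** **The plan's own figure.** No power or precision figure is given for the implementation outcomes. The one design figure is 80% power for the primary clinical outcome, from 46 cases per step per hospital, 9 hospitals, 33% versus 13%, intra-cluster correlation 0.121 and cluster auto-correlation 0.328. The average binomial variance is (0.33 × 0.67 + 0.13 × 0.87) / 2 = (0.2211 + 0.1131) / 2 = 0.1671. A generalised least squares calculation with three sequences of three hospitals and six 6-month periods returns power 0.800 (0.773 with four periods). The figure reproduces, and nothing below depends on it.

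**The two analyses side by side.**

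| Feature | Secondary hypotheses | Implementation outcomes |
|---|---|---|
| Type | Mixed model, conditional on hospital and hospital-by-time effects | Marginal GEE, autoregressive working correlation, sandwich errors |
| Link | Logit in model (1); no other link named | Whichever is appropriate |
| Time | Fixed effects θ_t | Month |
| Treatment | One constant δ | Group plus group-by-month |
| Tested term | δ | Interaction |
| Status | Inferential | Called descriptive, then judged by a p value |

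**Do they test the same thing?** Write g for the link and μ for the mean outcome.

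- Analogue of model (1): g(μ) = γ + θ_t + A·δ + random effects. The contrast between conditions is δ at every time.
- GEE: g(μ) = β0 + β1·G + β2·M + β3·G·M. The contrast at month M is β1 + β3·M, and the test is of β3 = 0.

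Suppose facilitation raises the monthly rate of order-set changes by a fixed amount on the link scale and holds it there, which is what model (1) assumes. Then β1 + β3·M = δ for every M, so β1 = δ and β3 = 0. The interaction test is then under its null however large δ is, and it would reject only at its nominal error rate. If month is entered as categories, the interaction terms are again all zero.

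The reverse can also happen. If an early loss is offset by a later gain, δ averages to about zero while β3 does not.

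The conflict does not come only from the conditional-versus-marginal distinction. With a log or identity link and normal random effects independent of treatment, the treatment coefficient is the same in both forms. It is the tested term that differs.

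**Does the logit suit penetration?** A link acts on the mean. The logit, log(μ / (1 − μ)), needs 0 < μ < 1. A mean of 3 order sets, for example, would give 3 / (1 − 3) = −1.5, which has no logarithm. Nothing in the article holds the mean count below 1. The patient index in model (1) also has no counterpart for a hospital-level count or for a survey of staff.

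**The case against.** The best defence is that the section written for these outcomes governs. The Secondary hypotheses text sits under Clinical outcomes, and its two listed hypotheses concern only surgical site infection and C. difficile infection. The implementation outcomes appear there in one trailing phrase. The other section is detailed, and its choice of an appropriate link already accommodates a count. That is the sensible reading, and the fix adopts it. It remains an inference, because the article states both rules and ranks neither.

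Three stronger readings are tempting, and the document does not support them.

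- **That the first model cannot be fitted.** The text says the model is analogous to model (1). The same linear predictor with a log or other link would be fittable. Only the logit form taken literally is unsuitable for a count. Nor is it an argument that an observed count has no finite logit: observed zeros and ones in any logistic regression have none either.
- **That the logit is undefined for the survey scores.** The article does not give their scale or scoring, and ordinal or dichotomised scores can be modelled with logit-type links.
- **That the choice would be made after the data are seen.** A separate analysis plan may settle it. A late choice is a risk and is not shown.

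An article may also leave link and distribution to a fuller plan. That answers a complaint about missing detail, but not two stated rules that conflict.

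**Conclusion.** The inconsistency holds and is modest in size. The implementation outcomes, including the primary one, have two stated inferential analyses that test different quantities and can disagree, with no precedence. The sustained shift that model (1) assumes is the very pattern that the GEE's tested term cannot detect. Judging the groups by that interaction p value also sits badly with calling the analysis descriptive and unpowered for group differences.

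The conclusion rests on the written text and the algebra above. It takes the group indicator to mean the condition in force, control or facilitation, and it needs no assumption about the survey scales. A reader might infer that the trial's main conclusion is at risk, but it is not: the primary clinical analysis has its own model, and the sample size is based on the primary outcome only.

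**What to change.** 1. In Secondary hypotheses, delete the reference to implementation outcomes at the end of the sentence on what replaces the probability term. The model analogous to model (1) then covers only surgical site infection and C. difficile infection, and the Implementation outcomes section governs the rest.
2. In Implementation outcomes, specify a count model with a log link for penetration.
3. In the same section, report the group contrasts as descriptive estimates with intervals, and drop the interaction p value as the criterion for whether the groups differ. This brings the analysis into line with the section's opening.

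The cost is wording only. No data collection, sample size or primary analysis changes.
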